## Abstract

**Background:**

Cardiovascular disease (CVD) is the major cause of death after renal transplantation. Not only conventional CVD risk factors, but also transplant-specific risk factors can influence the development of CVD in kidney transplant recipients.

The main objective of this study will be to determine the incidence of post-transplant CVD after renal transplantation and related factors. A secondary objective will be to examine the ability of standard cardiovascular risk scores (Framingham, Regicor, SCORE, and DORICA) to predict post-transplantation cardiovascular events in renal transplant recipients, and to develop a new score for predicting the risk of CVD after kidney transplantation.

**Methods/Design:**

Observational prospective cohort study of all kidney transplant recipients in the A Coruña Hospital (Spain) in the period 1981-2008 (2059 transplants corresponding to 1794 patients).

The variables included will be: donor and recipient characteristics, chronic kidney disease-related risk factors, pre-transplant and post-transplant cardiovascular risk factors, routine biochemistry, and immunosuppressive, antihypertensive and lipid-lowering treatment. The events studied in the follow-up will be: patient and graft survival, acute rejection episodes and cardiovascular events (myocardial infarction, invasive coronary artery therapy, cerebral vascular events, new-onset angina, congestive heart failure, rhythm disturbances and peripheral vascular disease).

Four cardiovascular risk scores were calculated at the time of transplantation: the Framingham score, the European Systematic Coronary Risk Evaluation (SCORE) equation, and the REGICOR (Registre Gironí del COR (Gerona Heart Registry)), and DORICA (Dyslipidemia, Obesity, and Cardiovascular Risk) functions.

The cumulative incidence of cardiovascular events will be analyzed by competing risk survival methods. The clinical relevance of different variables will be calculated using the ARR (Absolute Risk Reduction), RRR (Relative Risk Reduction) and NNT (Number Needed to Treat).

The ability of different cardiovascular risk scores to predict cardiovascular events will be analyzed by using the c index and the area under ROC curves. Based on the competing risks analysis, a nomogram to predict the probability of cardiovascular events after kidney transplantation will be developed.

**Discussion:**

This study will make it possible to determine the post-transplant incidence of cardiovascular events in a large cohort of renal transplant recipients in Spain, to confirm the relationship between traditional and transplant-specific cardiovascular risk factors and CVD, and to develop a score to predict the risk of CVD in these patients.

## Background

Cardiovascular disease (CVD) is one of the most common complications after renal transplantation, with a considerably higher incidence than in the general population [1]. Although in recent years some authors have documented a significant reduction in cardiovascular death after kidney transplantation [2], today CVD is still the major known cause of death in kidney transplant patients [3].

In addition to the conventional CVD risk factors (such as obesity, smoking habits, diabetes, hypertension or dyslipidemia), several other factors seem to influence the high incidence of cardiovascular events in renal transplant patients [4,5]. These include, amongst others, the duration of prior dialysis [6-8], graft function after transplantation [9-11], hyperhomocysteinemia [12-16], elevated inflammatory markers [16-18], proteinuria [19-22], acute rejection episodes [23], post-transplant diabetes mellitus [6,24-27], and the toxic effects derived from the use of immunosuppressant medications and other drugs [28,29].

Therefore, when evaluating patients prior to kidney transplantation, special attention should be given to cardiovascular risk factors. To determine the individual risk of cardiovascular events, risk scores have been established in general populations, such as the Framingham Heart Study score [30,31], the Regicor (Framingham calibrated to Spain) [32], SCORE [33] or DORICA [34]. However, the validity of these equations in more selected populations, such as those of transplant patients, is not well established. In renal transplant recipients, the Framingham score does not seem to accurately predict the individual cardiovascular risk, leading to an underestimation of the cardiovascular event rates [4,16]. A recent study has corroborated the poor predictive accuracy of the Framingham score in these patients, indicating the need to consider new predictive models that incorporate both traditional and non-traditional cardiovascular risk factors [35].

Determining the incidence of cardiovascular events after a kidney transplant and the associated risk factors is therefore important in order to inform physicians of the need for CVD screening and prevention as part of the transplant evaluation [36]. Moreover, an accurate estimation of a patient's risk of cardiovascular disease could make it possible to identify people at high risk of suffering a cardiovascular event, and intervene proactively before they develop the disease.

This project was designed with three main objectives: firstly, to determine the incidence of post-transplant cardiovascular events after renal transplantation and related factors; secondly, to examine the ability of established cardiovascular risk scores (Framingham, Regicor, SCORE, and DORICA) to predict post-transplantation cardiovascular events in renal transplant recipients; and finally, to develop and validate a cardiovascular risk score to predict the risk of developing a cardiovascular event after kidney transplantation.

## Methods/Design

### Design and study population

Observational, retrospective and prospective cohort study of all adult (> 18 years) patients who underwent primary or repeated kidney transplantation with a graft from a cadaveric or living donor in the A Coruña Hospital (northwest Spain) between 1 January 1981 and 31 December 2008. Patients who had undergone simultaneous kidney-pancreas transplantation will be excluded from the analysis.

### Measurements

All the variables that will be recorded for each one of the patients included in the study are summarized in Additional file 1: Table S1.

Characteristics recorded at the time of transplantation include donor and recipient age and gender, body weight, height, body mass index (weight in kilograms divided by the height in meters squared), primary cause of renal failure (type I diabetes mellitus, type II diabetes mellitus, primary glomerulonephritis, nephrosclerosis including hypertension and renovascular disease, polycystic kidney disease, systemic lupus erythematosus, and others), cold ischemia time, type of dialysis prior to transplant (hemodialysis or peritoneal dialysis), total duration of renal replacement therapy before transplantation, and previous transplants. The date of transplantation and the type of donor (a deceased or living donor) will also be recorded.

Information about other traditional cardiovascular risk factors at the time of transplantation will also be collected, including history of tobacco smoking, hypertension, hypercholesterolemia, left ventricular hypertrophy, prior diabetes and a history of cerebrovascular disease (transient ischemic attacks and strokes), peripheral vascular disease (revascularization procedures and amputations) and malignancies prior to transplantation.

After transplantation, episodes of acute rejection and infections will be registered, together with the patient's smoking status, new-onset diabetes and diagnosis of left ventricle hypertrophy. Biochemical parameters will be collected during the post-transplantation follow-up at week 1, week 2, month 1, month 3, month 6, and yearly thereafter. These will include white blood counts, hematocrit, haemoglobin, cholesterol, high-density lipoprotein (HDL) cholesterol, low-density lipoprotein (LDL) cholesterol, triglycerides, creatinine levels and 24-hour proteinuria. At the same time intervals, systolic and diastolic blood pressure will be recorded. Renal function will be estimated using the Cockcroft-Gault formula [37] and the modified Modification of Diet in Renal Disease (MDRD) equation [38]. In the analysis of factors predicting new post-transplant cardiovascular events, the average of laboratory and blood pressure values recorded before the event will be considered.

For the analysis, the cut-points defining the control of each risk factor will be taken from the European Guidelines on CVD prevention [39]. For estimates of dyslipidemia control based on LDL, HDL cholesterol and triglycerides, we will use the cut-points agreed in the consensus statement from the American Diabetes Association and the American College of Cardiology Foundation [40].

The initial immunosuppressive regimen of the patients and changes in treatment during follow-up will be recorded. Dosage of immunosuppressive drugs will also be registered after transplantation at week 1, week 2, months 1, 3 and 6, and yearly thereafter. The use of antihypertensive and lipid-lowering drugs after transplantation will also be registered at the same times.

Post-transplant cardiovascular events are defined as the presence of myocardial infarction, invasive coronary artery therapy, cerebral vascular events (stroke and transient ischemic attacks), new-onset angina, congestive heart failure, rhythm disturbances (ventricular tachycardia, atrial fibrillation and the need for a pacemaker), and peripheral vascular disease. Peripheral vascular disease is defined as the need for invasive therapy or conservatively managed limb gangrene.

Patients will be followed-up from the date of renal transplantation until death or their return to dialysis.

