### Statistical analysis

A descriptive analysis of the variables recorded will be performed. Observed frequencies and percentages will be used for qualitative variables, with their 95% confidence interval, and the mean and standard deviation or median and interquartilic range for quantitative variables.

The primary outcome for this study will be the estimation of the probability of cardiovascular disease in the presence of other competitive events in renal transplant patients. The cumulative incidence of cardiovascular events after kidney transplantation will be analyzed by competing risk survival methods, where each subject is at risk of failure from different causes. Therefore, each patient will be classified in four states of interest (alive with functioning graft, death, graft failure and cardiovascular disease).

Cumulative incidence functions will be used to compare the observed incidence of events between groups [48]. The cumulative incidence function regression model of Fine and Gray will be used for multiple regression analyses [49]. Additionally, the clinical relevance of different variables will be evaluated using the ARR (Absolute Risk Reduction), RRR (Relative Risk Reduction) and NNT (Number Needed to Treat).

In order to analyze the ability of each of the four cardiovascular risk scores to predict cardiovascular events rates, the concordance c index [50] and the area under the receiver-operating characteristic (ROC) curves, using a time-dependent approach [51], will be calculated. To calibrate the scores, relative risk ratios for observed-to-predicted event rates will be computed, and the Hosmer-Lemeshow test will be applied.

Based on the competing risks analysis, a nomogram to estimate the probability of cardiovascular events after kidney transplantation will be developed. The objective is to use the conditional cumulative incidence function to provide a patient-specific prediction of the probability of failure in the setting of competing risks.

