## Discussion

In recent years, several important changes have occurred in the management of kidney transplant patients that have been associated with an improvement in rejection rates and early graft survival [53]. Therefore, attention is now focusing on improving long-term transplant outcomes [3]. Renal dysfunction and increased cardiovascular risk are some of the factors that have a negative impact on long-term graft and patient survival. Although some authors have documented a reduction in CVD-related deaths in kidney transplant recipients in recent years, CVD is still the leading cause of death in patients with a functioning allograft [2].

Several studies have analyzed the risk factors connected with the incidence of cardiovascular events after kidney transplantation [4-29]. However, the role of some novel risk factors remains unclear. Furthermore, most of the previous studies are based on retrospective analyses of registry data, which contains information only on baseline data at the time of transplantation and the immediate post-transplantation follow-up. As a result, long-term follow-up data on clinical, biochemical and treatment covariates after transplantation is not always available.

This study will allow us to determine the post-transplant incidence of cardiovascular events in a cohort of renal transplant recipients in Spain, as well as to confirm the relationship between some CVD risk factors and the occurrence of a cardiovascular event in these patients. The development of a specific CVD risk score for kidney transplant recipients would make it possible to identify patients at high risk for coronary events at the time of transplantation, or shortly after the transplant. Therefore, this risk assessment could be used to recommend lifestyle changes for patients, to initiate appropriate treatment, or to redesign the immunosuppressive regimens for the prevention of primary or recurrent cardiovascular events in kidney transplant patients. The majority of studies use survival analysis strategies with the methodology of Kaplan and Meier. As this methodology may lead to overestimating the likelihood of the occurrence of the events of interest, we propose a competitive risk analysis in order to study the prognosis of these patients [48,49].

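### Averaging laboratory and blood-pressure values up to the event makes the predictor depend on event-free time, so markers that drift after transplantation can look like false risk factors

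*Protocol article*

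**What the plan says.** The rule is in the Protocol article, Measurements. It applies "In the analysis of factors predicting new post-transplant cardiovascular events", and there "the average of laboratory and blood pressure values recorded before the event will be considered". The same section gives the schedule: "Biochemical parameters will be collected during the post-transplantation follow-up at week 1, week 2, month 1, month 3, month 6, and yearly thereafter". Blood pressure follows it: "At the same time intervals, systolic and diastolic blood pressure will be recorded". That makes five values in the first six months and one a year afterwards.

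The time axis is also in Measurements: "Patients will be followed-up from the date of renal transplantation until death or their return to dialysis". Under Statistical analysis, "The cumulative incidence function regression model of Fine and Gray will be used for multiple regression analyses", and "Based on the competing risks analysis, a nomogram to estimate the probability of cardiovascular events after kidney transplantation will be developed". The Discussion says that the new score should "identify patients at high risk for coronary events at the time of transplantation, or shortly after the transplant".

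The article states no landmark, no time-updated covariate and no fixed averaging window. It does not say where the window ends for a patient who never has an event.

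**The concern.** The averaging window closes at the outcome, while the patient is counted at risk from transplantation. If one average per patient enters the model, its value reflects how long that patient remained event-free. A patient with an event at month 7 contributes only the five early values. A patient event-free for 15 years contributes mostly yearly values from stable follow-up. Any systematic drift in the marker then separates the two, even when the marker has no bearing on risk.

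This touches two of the three objectives: the factors related to cardiovascular events, and the new score. The planned 1000 bootstrap replications would not help. They address overfitting, and every resample carries the same covariate definition.

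There is also a practical problem. An average that runs up to a future event does not exist when the score is to be applied.

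**Working it through.** **1. The plan's own figure.** The article sizes the study for a relative risk of 1.33, 50% exposure, 78% censoring, two-sided α 0.05 and 80% power. By Schoenfeld's formula, events = (1.960 + 0.842)² / (0.25 × ln(1.33)²) = 386.04. Dividing by 0.22 gives 1754.7, so the stated 1755 reproduces. It does not depend on this point.

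**2. What the rule does to two patients with identical biology.** Let the marker's population mean at time v years be a × exp(−v/0.25), an assumed early fall of a SD units. Visits follow the protocol schedule.

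- Event at month 7: the five visit values (a = 1) are 0.926, 0.858, 0.717, 0.368 and 0.135. Their sum is 3.004 and their mean 0.60.
- Event-free just past 15 years: the sum is 3.004 + 0.018 (year 1) + about 0 = 3.022 over 20 visits, mean 0.15.

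The rule places these patients 0.45 SD apart although the marker has no effect. With an assumed rise of 0.05 SD per year, the mean visit times are 0.891/5 = 0.178 years and (0.891 + 120)/20 = 6.04 years. The averages are therefore 0.01 and 0.30 SD, a gap of 0.29 SD in the other direction.

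**3. Null simulations.** From the article: 1794 patients, the visit schedule, and 22.2% events at five years, i.e. a constant hazard of −ln(1 − 0.222)/5 = 0.050 per year. Assumed: competing hazard 5% per year and the marker trends. The marker never affects the event. The Cox runs also assumed between-patient SD 1, visit SD 1 and administrative censoring uniform over 1 to 28 years, with about 170-180 replicates per scenario.

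False-positive rates for the average-before-event covariate are below. The Fine and Gray column gives the range over two sets of runs, except for the 2 SD fall, which was in one set. One set used 100 replicates per scenario. The Cox hazard ratio is per SD.

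| Assumed trend | Fine and Gray | Cox (hazard ratio) |
|---|---|---|
| None | 5-7% | 6% (1.00) |
| Early fall 0.5 SD | 13-23% | 40% |
| Rise 0.05 SD/year | 23-31% | 86% (0.89) |
| Early fall 1 SD | 53-63% | 88% (1.15) |
| Early fall 2 SD | 99% | 100% (1.34) |

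Under Fine and Gray, the 1 SD early fall gave a false subdistribution hazard ratio of 1.08 per SD. With the average dichotomised at its median, Fine and Gray rejected in 16%, 43% and 94% of runs for early falls of 0.5, 1 and 2 SD. The c index of this null marker reached 0.53-0.63 with early falls, where 0.50 is correct.

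**4. The alternatives under the same null.** A 1-year landmark average gave 3-6% rejections in one Fine and Gray set. In the Cox runs it gave a hazard ratio of 1.00 and 3-8% rejections, and a week-1 value gave 0.99-1.01 and 4-8%. With about 175 replicates the Monte Carlo standard error at 5% is √(0.05 × 0.95/175) = 1.6 points, so these fit the nominal level.

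**The case against.** The sentence is brief and the article condenses a fuller plan. A running mean, updated at each time point, also fits its wording and would not look ahead. Restricting to pre-event values has a sound purpose too: it keeps out values altered by the event itself. Both points are fair, and the bias is therefore conditional on the one-value-per-patient reading. Still, the article gives an affirmative rule and pairs it with a regression for which no time-updating is stated. A running mean would also not supply a value at transplantation for the score.

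The averaging rule is written for the risk-factor analysis, and no predictor list is given for the nomogram. That stands: use of the averages in the score is possible, not stated. The Discussion also allows use shortly after transplantation, so a short, fixed early window could feed the score. An average running to the event could not.

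The size rests on assumed trends. That stands as well. With no trend there is no bias, and under the planned Fine and Gray model the bias is smaller than under Cox. The article's guideline cut-points for risk-factor control may lead to categorised predictors. Dichotomising at the median reduced the false-positive rate but did not remove the problem.

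**Conclusion.** The point holds in conditional form. If each patient's pre-event average enters as a single value with time running from transplantation, a marker that drifts with time since transplantation can be falsely associated with cardiovascular disease and can appear to discriminate. Under Fine and Gray the false-positive rate runs from nominal with no trend, through 13-31% for small trends and 53-63% for a 1 SD early fall, to about 99% for a 2 SD early fall. The trends and the competing hazard are assumptions, because the article gives no trajectories.

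A reader might infer more than the article supports:

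- That every laboratory and blood-pressure result will be spurious. Only markers with a systematic trend are at risk, and near-certain rejection belongs to steep trends.
- That a false hazard ratio equals the effect the study is sized for. The Cox value of 1.34 is per SD under a 2 SD fall, whereas 1.33 refers to a binary exposure at 50% prevalence.
- That the nomogram is certainly affected. The article does not say that the averages enter it.
- That rejection, new-onset diabetes and left ventricular hypertrophy are mishandled in the same way. The article says only that they are recorded.

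The crude cumulative incidence, the four established scores (applied at transplantation) and the sample size are not affected.

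**What to change.** Replace the averaging rule in Measurements with two rules.

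- **Risk-factor analysis:** enter laboratory values and blood pressure as time-updated covariates (last value, or running mean up to time t) in start-stop cause-specific Cox models. This still excludes values recorded after the event and keeps the longitudinal data in use.
- **Fine and Gray and the nomogram:** use only values known at transplantation, or averaged over a fixed early window that is the same for everyone, with follow-up starting at the end of that window. State the landmark in advance.

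The repeated measurements are already scheduled for collection, so the cost is revised wording and some start-stop programming. Patients with an event before the landmark leave the landmark model, so its predictions apply only to those still event-free at that time.

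### An ordinary mean of laboratory and blood-pressure values over the front-loaded visit schedule heavily over-weights the first six months; the effect is material for raw creatinine and smaller for estimated renal function

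*Protocol article*

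**What the plan says.** The Measurements section sets a schedule and a derivation rule.

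- Schedule: laboratory values are taken "at week 1, week 2, month 1, month 3, month 6, and yearly thereafter". For blood pressure: "At the same time intervals, systolic and diastolic blood pressure will be recorded".
- Rule: "In the analysis of factors predicting new post-transplant cardiovascular events", "the average of laboratory and blood pressure values recorded before the event will be considered". No weighting and no first visit are given.
- Follow-up: "Patients will be followed-up from the date of renal transplantation until death or their return to dialysis". With transplants from 1981 to 2008, individual records can run from weeks to decades.

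The section also says that renal function will be estimated by the Cockcroft-Gault and MDRD formulas. The Discussion faults earlier registry work because it "contains information only on baseline data at the time of transplantation and the immediate post-transplantation follow-up". It wants the new score to "identify patients at high risk for coronary events at the time of transplantation, or shortly after the transplant".

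**The concern.** Taken in its ordinary sense, an average is the sum divided by the count, so each recorded value has the same weight. Under this schedule a week-1 value, which stands for a few days, counts as much as a yearly value, which stands for about a year. Creatinine at weeks 1 and 2 largely reflects how fast the graft recovers from surgery. The mean therefore mixes early graft recovery with settled function, in proportions set by the visit calendar.

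Two things are at stake for the Fine-Gray models and the nomogram. The association with settled function is attenuated, and part of any creatinine effect may really be an effect of early recovery. The mixture also differs between patients, because the early share falls as follow-up lengthens. The weighting problem is present even between two patients with equal follow-up, and it would persist in an average updated over time.

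**Working it through.** The plan gives no figure for this derivation, so there is none to reproduce. Its required sample size of 1755 does not depend on the point.

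**1. Share of values against share of time.** Inputs: the schedule in Measurements, all visits attended, yearly visits at whole years. Up to and including year k there are 5 + k values, of which 5 fall in the first six months, 3 in the first month and 2 in weeks 1-2.

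| Year k | Values | First six months: values / time | First month: values | Weeks 1-2: values / time |
|---|---|---|---|---|
| 2 | 7 | 5/7 = 71% / 0.5/2 = 25% | 3/7 = 43% | 2/7 = 29% / 1.9% |
| 5 | 10 | 5/10 = 50% / 0.5/5 = 10% | 3/10 = 30% | 2/10 = 20% / 0.8% |
| 10 | 15 | 5/15 = 33% / 0.5/10 = 5% | 3/15 = 20% | 2/15 = 13% / 0.4% |

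If each value is instead weighted by the interval between the midpoints to its neighbours, the first-six-month visits carry 15% at 5 years and 7.5% at 10 years. The first-month visits carry about 3% and 2%.

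**2. When early values are a majority.** First six months: 5/(5 + k) ≥ 1/2 when k ≤ 5, so until the year-6 visit. First month: 3/(5 + k) ≥ 1/2 when k ≤ 1, so only until the year-2 visit.

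**3. Dependence on follow-up.** The first-month share is 3/5 = 60% for an event at nine months and 20% at ten years.

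**4. Assumed pair of records over 5 years (creatinine, mg/dL).** A, slow start and good settled function: 7, 4, 1.8, 1.5, 1.4, then 1.4 yearly. B, chronically raised: 2.0, then 1.8 throughout.

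- Plain mean: A = (7 + 4 + 1.8 + 1.5 + 1.4 + 5 × 1.4)/10 = 22.7/10 = 2.27. B = (2.0 + 9 × 1.8)/10 = 18.2/10 = 1.82. A looks worse.
- Time-weighted mean (trapezoid area divided by time): A = 1.44, or 1.46 if the week-1 value is carried back to day 0. B = 1.80. B is worse.
- Plain mean of 1/creatinine, as a rough stand-in for estimated renal function (higher is better): A = 0.590, B = 0.550. A ranks better at 5 years, although it still ranks slightly worse at 1 to 2 years.

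**5. Simulation at fixed follow-up.** Assumptions: stable creatinine with median 1.5 mg/dL and log SD 0.3; slow initial function in 15-35% of patients, raising week 1 about 4.5-fold and week 2 about 2.7-fold; 10% visit noise. The measure is the squared correlation of the log summary with log stable creatinine.

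| Summary | 2 years | 5 years |
|---|---|---|
| Plain mean of creatinine | 54-73% | roughly 68-82% |
| Time-weighted mean of creatinine | 96-97% | 98% |
| Plain mean of 1/creatinine | 84-90% | about 92-95% |

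The ranges cover the spread in slow initial function and different handling of month 1. A month-1 rise of 1.3-fold takes the lower end at 5 years to 67%.

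**The case against.** The strongest reply has four parts.

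- **The weighting is not stated.** A condensed article may leave it to an analysis plan. This stands in part. Equal weighting is a reading, but it is the ordinary one, and the article chose to state a rule next to a schedule on which that rule performs poorly.
- **No long-term aim is stated for this average.** This stands. A reader might infer from the criticism of registry studies that the average is meant to capture a long-term level, or that the rule contradicts that criticism. The text supports neither: the study does collect yearly values, and the score is meant for use at or soon after transplantation, where early values carry relevant information.
- **Early values do not swamp the mean.** This also stands. A reader might conclude that the first weeks dominate it or that it fails to measure settled function. Weeks 1-2 supply only 20% of the values at 5 years, and even raw creatinine keeps most of the variance there. This is attenuation and mixing, not loss of the signal.
- **The harm depends on the scale.** The planned renal-function formulas are inverse in creatinine. On that scale the example no longer reverses at 5 years and the loss is modest. Raw creatinine is also collected, so the point remains for that variable. One constructed pair shows that a reversal can happen, not that it is typical.

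A further objection is that the same sentence has a more serious defect: the averaging window ends at the event, so the outcome defines the covariate, and patients without an event have no stated window. That is a separate problem, which time-weighting alone would not cure. Curing it would not cure the weighting either: at a one-year landmark, 5 of 6 values (83%) would still come from the first half of the year.

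**Conclusion.** The point holds as an over-weighting of the first six months: 71%, 50% and 33% of the values for 25%, 10% and 5% of the time at 2, 5 and 10 years, with a share that varies with follow-up. These shares follow from the schedule, given an unweighted mean and complete visits. Missed early visits in older records would lower them.

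The consequence is material for raw creatinine, smaller for estimated renal function and unknown for blood pressure, lipids and proteinuria. The variance figures rest on the assumed frequency and size of slow initial function, which the article does not give. The rule should be changed, but the point does not invalidate the study.

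**What to change.** In Measurements, replace the average with a time-weighted average: the area under the value-time curve divided by elapsed time. Compute it within one of two forms, so that the window is not defined by the event:

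- a landmark covariate, using values up to a fixed time in patients still event-free then, which also suits a score used soon after transplantation; or
- a time-updated covariate in a cause-specific model.

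Enter the week 1, week 2 and month 1 values as a separate early-graft-function covariate. The visit at which the average starts, for example month 3, is the analysts' choice and should be stated.

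The cost of the weighting change is about one sentence and a few lines of code, with no new data. The small downside is that events before the start visit must be modelled from transplant-time and early covariates only.
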